## Abstract

Improving health outcomes via sustained weight loss and maintenance requires advancing understanding of the metabolic, appetitive, and neurological alterations that counteract—and eventually halt—weight loss. Prior studies have demonstrated increased appetite as well as metabolic adaptations, such as increased energy efficiency, in response to weight loss. However, previous study designs utilized experimentally determined weight loss plateaus and did not investigate spontaneously occurring plateaus nor study participants in their natural, free-living, environments during weight loss. The *Assessing Diet, Appetite, and Physiology Throughout weight loss* (ADAPT) study was designed to address these limitations of prior research and elucidate mechanistic factors involved in spontaneous cessation of intentional weight loss in humans. ADAPT enrolls participants with obesity who undergo behavioral weight loss via a reduced calorie diet and increased physical activity. Participants’ daily weight is monitored remotely, and new analytic approaches identify weight-loss phases in real time so that study assessments can be targeted to each participants’ individualized trajectory during dynamic weight loss. Deep phenotyping of participants includes anthropometric, metabolic, neurophysiologic, and behavioral assessments; physical activity and physiologic monitoring via wearable devices; and serial sampling of biological tissues such as blood, adipose tissue, and muscle. In summary, the ADAPT study design is generating a uniquely informative and integrative dataset for deepening understanding of the biological mechanisms that halt behaviorally-induced weight loss and thereby limit its long-term health benefits for patients with obesity. NCT06174389.

## Introduction

Behavioral strategies for obesity treatment reliably result in weight loss and health benefits [1–3]. However, weight loss typically plateaus at ~7–10% of total body weight (a plateau phase [4]) and weight regain is common [4–6] limiting the ability of behavioral intervention strategies to modify obesity-related disease risk in a sustained manner. Improving health outcomes via sustained weight loss and maintenance requires advancing understanding of the metabolic, appetitive, and neurological alterations that counteract—and eventually halt—weight loss. Prior research has documented increased hunger, decreased satiety [7,8] and increased food intake after a period of weight loss [9]. Additional findings [10] demonstrate reduced satiety response in brain regions controlling reward and motivation, which may contribute to the biology of weight loss plateaus. Documented metabolic responses to weight loss include declines in total body [11–14] and resting energy expenditure [11,15,16] and increased skeletal muscle work efficiency [17,18].

Additionally, weight loss is a dynamic and individual process, but prior study designs have not adequately captured these characteristics. Early phase weight loss has been previously defined as rapid, of 4–6 weeks’ duration, and reflective of shifts in body water content more so than adipose reduction [19]. Active weight loss involves steady adipose depot depletion that eventually ends at a weight loss plateau (also called static phase [20]). Weight loss plateaus, while individually variable, reflect cessation of weight loss, are frequently involuntary, and are documented consistently in behavioral weight loss trials [4,5], chronic caloric restriction [21], pharmacologic studies [4,22], and bariatric surgery [23]. Physiologic adaptations that can be accentuated at the plateau phase include appetite stimulation [24,25] and reductions in resting energy expenditure (REE) [12,24,26,27]. Prior studies of weight-reduced plateaus have typically halted weight loss at an experimentally determined weight and then maintained a steady weight by prescribing participants a calorically controlled liquid maintenance diet [11,17,18,28–31]. These controlled designs are limited by not accurately characterizing the physiologic and neurologic adaptations opposing further weight loss at a spontaneously occurring plateau and are also unable to elucidate factors predicting cessation of weight loss since it is experimentally determined. Further, in recent years, the capability to remotely collect real-time data during weight loss has advanced, but investigations of behavioral weight loss have yet to fully exploit these technologies. Study designs that adaptively assess physiological changes in multiple tissue types as the pace and extent of weight loss evolve over time could provide novel insights into the driving factors underlying weight loss plateaus in humans.

The *Assessing Diet, Appetite, and Physiology Throughout weight loss* (ADAPT) study was designed to address limitations of prior research. Novel approaches were integrated into the protocol, including multi-modal phenotyping of appetite and energy expenditure through biological sampling and neuroimaging in combination with behavioral assessments. Importantly, by using remotely assessed daily weights to characterize each participant’s weight-loss trajectory, ADAPT individualizes timing of biological assessments according to defined phases of weight loss, including a weight-loss plateau. This adaptive design and phase-based approach distinguishes ADAPT from prior studies that relied on fixed, predetermined time points.

The overarching hypothesis of ADAPT is that an involuntary weight loss plateau is characterized by accentuated changes in bioenergetics and neuro-physiology that thwart efforts at additional weight loss and, ultimately, favor weight regain [Fig 1]. ADAPT also investigates predictors of entering into a weight loss plateau that could be mechanistically related to cessation and/or the degree of weight loss in response to behavioral weight loss. To investigate these hypotheses, the study implements a remotely delivered group behavioral weight loss program augmented by individual support to stimulate weight loss. We combine this program with real-time monitoring and individually timed outcome assessments to study 90 adults with obesity at baseline, and re-evaluating those who enter active weight loss and plateau phases, as defined by the study protocol. The specific aims of this research are threefold: 1) to test if an involuntary weight loss plateau is distinguished metabolically from other phases of weight loss by alterations in cellular bioenergetics across multiple tissue types, 2) to test for neurophysiologic changes consistent with reduced satiety at a weight loss plateau and their relation to metabolism, and 3) to explore predictors of a weight loss plateau. We hypothesize that peripheral blood mononuclear cells, myofibers and adipocytes obtained during the plateau phase will show reductions in mitochondrial respiratory capacity and/or improved coupling relative to baseline and active weight loss. We further hypothesize that the central satiety response will be reduced from baseline at a weight loss plateau, activation in inhibitory control regions involved in self-regulation will be enhanced, and both will correlate with suppressed tissue-level and whole-body metabolism [Fig 1]. Finally, we hypothesize that our exploratory predictive analyses will identify potential behavioral, neurophysiologic, and bioenergetic predictors of early entry into an involuntary weight loss plateau that would be appropriate targets for future research or interventions.

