### Statistical analysis plan

#### Aim 1.

Primary outcomes are oxidative phosphorylation and maximal respiratory capacity in T-cells, and permeabilized muscle fibers, the latter with fatty acid oxidation and complex I substrate. Secondary outcomes include T-cell and permeabilized muscle fibers uncoupling (proton leak respiration), adipose tissue mitochondrial respiratory capacity and coupling, UCP-1 expression, and inflammatory and lipolytic markers. As a prelude to inferential testing, linear regression will assess change in each measure as a function of potential confounding baseline covariates including % body fat, age, and sex as well as resting energy expenditure. Linear mixed models (adjusted for baseline confounders if needed) will be used to test for a main effect of time (baseline, active weight loss, plateau), followed by Bonferroni-adjusted formal *post hoc* testing to assess differences between phases and evaluate if a weight loss plateau represents a distinct metabolic state. We will then explore *evidence of cross talk* among T-cells, muscle, adipose tissue, and brain measures of appetite (See Aim 2 below). For measures that are changed from baseline by weight loss, we will perform linear regression amongst outcomes of the change from baseline to active weight loss or weight loss plateau. *Implications for weight maintenance* will be explored via linear regression of % weight change from plateau to 18 mo. as a function of the change in primary and secondary metabolic measures at plateau phase from baseline, adjusting for time between plateau and end of follow-up. Secondary analyses will use values measured at plateau (not change). Stratified analyses will assess sex as a biological variable. A sample size of N = 40 at active weight loss and plateau provides 99% power to detect within-subject differences between baseline and plateau and end of follow up for primary outcomes.

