#### Aim 3.

The primary outcomes of interest being explored in Aim 3 are entry into a weight loss plateau (Yes/No) and time from baseline (beginning of behavioral weight loss program) to plateau entry (continuous). Entry into a weight loss plateau will be defined as the 1) day at which a subject met weight loss plateau criteria during real-time monitoring or 2) first day of a weight loss plateau identified via threshold regression modeling at study completion. *A priori* predictors of interest for Aim 3 are based on available literature and our own findings and include the slope of the first active weight loss period [64]; trends over time in craving for carbohydrates/starches, dietary restraint, and disinhibition [65]; changes in T-cell and muscle maximal respiratory capacity; fasting ghrelin [66]; and baseline central satiety response, mediobasal hypothalamic T2 relaxation time [67], leptin [28] concentrations, and HOMA-IR [68]. Other predictors (i.e., inhibitory control) may be tested based on the findings of Aims 1 and 2; remaining predictors will be considered exploratory. Analyses will include only participants who achieved active weight loss. Fully adjusted models will include baseline or change in % body fat. Sensitivity analyses will be completed to evaluate whether excluding participants not achieving adherence will have the same or better predictive capabilities. A sample size of N = 40 participants who achieve active weight loss provides 91% power to detect effect sizes of R^2^ ≥ 0.36 at P < 0.05 for continuous outcomes.

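### Aim 1's Bonferroni step after the three-phase test is valid but more conservative than per-outcome error control requires; gated pairwise tests at 0.05 would recover power for showing both plateau contrasts

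*Protocol article*

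**What the plan says.** The Introduction hypothesises that cells and tissue taken at plateau "will show reductions in mitochondrial respiratory capacity and/or improved coupling relative to baseline and active weight loss". Two contrasts are therefore needed: plateau against baseline, and plateau against active weight loss.

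Aim 1 of the Statistical analysis plan fixes the procedure. Linear mixed models "will be used to test for a main effect of time (baseline, active weight loss, plateau"). The pairwise step comes next in the same sentence, where the phase test is said to be "followed by Bonferroni-adjusted formal *post hoc* testing to assess differences between phases". The stated purpose includes to "evaluate if a weight loss plateau represents a distinct metabolic state". Aim 1 does not say how many comparisons the Bonferroni step covers, whether the pairwise tests run only after a significant phase test, or what alpha applies.

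On power, Aim 1 says: "A sample size of N = 40 at active weight loss and plateau provides 99% power to detect within-subject differences", naming baseline against plateau (and end of follow-up). No effect size, standard deviation or within-person correlation accompanies the figure, and no power is given for plateau against active weight loss. There are several primary outcomes: "Primary outcomes are oxidative phosphorylation and maximal respiratory capacity in T-cells, and permeabilized muscle fibers". The Bonferroni step is described for phases, not for outcomes.

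**The concern.** With three phases, if any two pairwise equalities are true, all three phases are equal. The only hypothesis above the single pairs is therefore the global null, which the phase test already addresses. If that test is passed at 0.05, each pair can be tested at 0.05 without raising the family-wise error for that outcome. Adding Bonferroni pays twice for the same error.

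The claim that plateau is distinct also needs both plateau contrasts to succeed. Testing each at 0.05 already holds that joint claim at or below 5%.

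The price falls mainly on plateau against active weight loss, which separates a plateau from weight loss in general. If active weight loss lies between baseline and plateau, this difference is smaller than the one for which power is quoted. A real plateau-specific change could then be missed more often than necessary. Extra participants are costly, since only those who reach a phase contribute and each visit involves biopsies.

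**Working it through.** **Inputs.** Three phases and N = 40 are from Aim 1. Two-sided alpha of 0.05 is assumed, because the article states it only for Aim 3 ("provides 91% power to detect effect sizes of R^2^ ≥ 0.36 at P < 0.05 for continuous outcomes"). The number of Bonferroni comparisons m is assumed to be 3 (all pairs; 0.05/3 = 0.0167), with m = 2 as the alternative. Simulations assume complete data and equal variances unless stated. Effects are in SDs of the within-person difference.

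**The plan's own figure.** The 99% cannot be reproduced without an effect size. Solving a paired t test (n = 40) backwards, 99% power corresponds to a difference of 0.695 at alpha 0.05 or 0.776 at 0.0167. If 0.695 was meant, power at 0.0167 is 96.7%, and 50 people would be needed to return to 99% (1 − 40/50 = 20%).

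**Family-wise error within one outcome (simulation, N = 40).**

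| Procedure | All phases equal | One phase differs |
|---|---|---|
| Phase test at 0.05, then pairs at 0.05 | 4.9–5.2% | 4.8–5.1% |
| Phase test at 0.05, then Bonferroni (m = 3) | 4.1–4.4% | 1.6–1.8% |
| Pairs at 0.05, no phase test | about 12% | about 5% |

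**Cost for a single contrast, ignoring the gate.** Sample ratio = ((z(1 − 0.025/m) + z(power)) / (z(0.975) + z(power)))²; share lost = 1 − 1/ratio.

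- m = 3, 80% power: ((2.394 + 0.842)/(1.960 + 0.842))² = 1.334, so 25.0%.
- m = 3, 99% power: ((2.394 + 2.326)/(1.960 + 2.326))² = 1.213, so 17.5%.
- m = 2: ratios 1.211 and 1.136, so 17.4% at 80% power and 11.9% at 99%.

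By paired t test, a difference of 0.454 has 80% power with 40 people at 0.05. At 0.0167 it has 64.5% power and needs 54 people.

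**Cost for showing both plateau contrasts, gate kept in both procedures, m = 3 (simulated search over n, pooled error).**

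| Pattern | Power | n without Bonferroni | n with | Share lost |
|---|---|---|---|---|
| Active equals baseline | 80% | 50 | 64 | 22% |
| Active equals baseline | 99% | 103 | 123 | 16% |
| Active midway | 80% | 50 | 68 | 26.5% |
| Active midway | 99% | 115 | 142 | 19% |

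For plateau against baseline alone at 80% power the loss is smaller, because the gate itself limits power: 17–19% if active equals baseline, about 7% if active lies midway.

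**Power at N = 40 for both contrasts (contrast-specific errors, m = 3).** With plateau–baseline 0.8 and plateau–active 0.45, power is about 64% with Bonferroni and 79–80% without. With plateau–active 0.4 it is 51–52% and 69%. If plateau–baseline is 0.695 and active lies midway, power for plateau against active is 39–41% with Bonferroni and 57–58% without.

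**Validity of each pair.** With an assumed twofold SD at plateau and a pooled error term, gated unadjusted pairs reached 8.1% family-wise error. With contrast-specific errors they stayed at 5.0%.

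**Without a gate.** A Holm–Shaffer step-down tests the smallest of the three p-values at 0.0167 and, if it passes, the other two at 0.05. It gave 4.4% error with all phases equal and 5.0–5.1% with one phase differing. Power for both contrasts was 79% and 69% in the first two power scenarios above.

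**The case against.** The plan contains no error here. Bonferroni comparisons after a mixed-model phase test are standard and valid. That stands: the point is one of efficiency.

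A reader might infer that the Bonferroni step does nothing for error control. The text does not support this, because it says only that the pairwise tests follow the phase test, not that they depend on it. Without a gate, unadjusted pairs give about 12% error when all phases are equal, so Bonferroni may be what controls error as written. The proposal therefore has to add the gate or use a step-down.

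A reader might also infer a flat loss of a quarter of the sample. That needs three comparisons and 80% power, neither of which Aim 1 states. At the article's 99% the loss is smaller, and for plateau against baseline alone smaller still.

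Two further objections stand as limits. Pooled errors can break the guarantee when variances differ between phases. And the Bonferroni step incidentally restrains false positives across outcomes: with four independent outcomes, each with one phase differing, the chance of any false positive is about 1 − 0.983⁴ = 6.6% with it and 1 − 0.95⁴ = 18.5% at 5% each. Four and independence are illustrative; positive correlation would lower both figures.

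**Conclusion.** Aim 1's procedure is valid but needlessly conservative within each outcome. Assuming three adjusted comparisons, it costs the equivalent of about 16–19% of the sample at 99% power, and 22–27% at 80% power, for showing both plateau contrasts. If only two comparisons are adjusted, the cost for a single contrast is about 12–17%. These figures rest on an assumed alpha of 0.05, complete data and equal variances.

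The documents do not support reading this as an invalid analysis, nor as proof that the 99% power statement is wrong: the inputs to that statement are not given, and it does not address plateau against active weight loss. The point is worth acting on because a more powerful procedure with the same per-outcome error control is available at almost no cost.

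**What to change.** Before the phase comparisons are examined, state in Aim 1 that:

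- pairwise phase contrasts are tested only if the three-level phase test is significant at 0.05;
- each pair is then tested at 0.05 with contrast-specific, not pooled, standard errors (for example from an unstructured within-person covariance);
- plateau is called distinct only if plateau against baseline and plateau against active weight loss are both significant.

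If no gate is wanted, a Holm–Shaffer step-down over the three pairs gives the same per-outcome control and nearly the same power.

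This takes a sentence or two and no extra data. The downside is that control is per outcome, so the chance of any false positive across Aim 1's primary outcomes is higher than under the present step. If alpha is divided across outcomes, the same closure applies within each outcome's share.

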**Fig 1 pone.0354678.g001:**
[figure not shown]
Conceptual model of the ADAPT study. Behavioral weight loss involves lifestyle modifications sufficient to cause negative energy balance and weight loss. A substantial percentage of individuals undergoing behavioral weight loss will experience a weight loss plateau—an involuntary cessation of weight loss and restored energy balance at a reduced weight. The ADAPT study is designed to assess physiological changes during weight loss in real-time. The hypothesized changes in energy efficiency and appetite could make achieving additional weight loss more challenging and promote involuntary weight regain.

## Materials and methods

### Study design and setting

ADAPT is a single group, longitudinal basic experimental study in humans [Fig 2]. It uses a behavioral weight loss program in participants with obesity to evoke entry into different phases of weight loss at which mechanistic outcomes are assessed [Fig 3]. The program is based on the PreventT2 curriculum [32,33] and involves group instruction and personalized coaching on reducing caloric intake to an individualized goal and increasing physical activity. Outcomes are assessed at study visits that are aligned with participants’ active weight loss and plateau phases. Study visit procedures provide comprehensive phenotyping of energy balance, behavior, and neurophysiological outcomes and include anthropometrics, behavioral questionnaires, physical activity monitoring via wearable device, daily remote weighing, functional and structural magnetic resonance imaging of the brain, fasting and serial blood draws during intake of a standardized meal, adipose tissue and muscle biopsies, indirect calorimetry, and body composition by dual x-ray absorptiometry (DXA). Planned analyses will compare bioenergetic, neurophysiologic, and hormonal outcomes between baseline and phases of weight loss. ADAPT takes place in the greater Puget Sound region of Washington state. In-person study visits occur at the University of Washington and Fred Hutchinson Cancer Center. All procedures used in this study adhered to the principles of the Declaration of Helsinki. The University of Washington’s Institutional Review Board approved of the study and its procedures with concurrence from the Fred Hutch Cancer Center IRB. All participants signed written informed consent.

**Fig 2 pone.0354678.g002:**
[figure not shown]
SPIRIT schedule of enrollment and assessments. Assessments in gray boxes occur at individualized time points aligned with phases of weight loss.

**Fig 3 pone.0354678.g003:**
[figure not shown]
Mechanisms of physiological changes associated with weight loss plateau are investigated in the ADAPT study. A behavioral weight loss program is used to evoke entry into different phases of weight loss at which mechanistic outcomes will be compared. Phenotyping for the state of energy expenditure includes obtaining peripheral blood mononuclear cells (PBMCs), muscle (myofibers), and adipose tissue specimens, as well as measures of whole-body resting energy expenditure by indirect calorimetry. We will examine each tissue type individually and also investigate how tissue “cross talk” among PBMCs (specifically T-cells), muscle, and adipose tissue contributes to systemic changes in bioenergetics. To assess the neurophysiology of appetite, brain responses in regions governing appetite, reward, and self-regulatory capacity are assessed by functional magnetic resonance imaging (fMRI) before and after a meal. fMRI is used to assess changes in the central satiety response at a weight loss plateau as well as activation in inhibitory control regions. Relationships of neurophysiologic outcomes with eating behavior, inhibitory control, gut hormones, brain structure, weight regain, and tissue-level and whole-body metabolism will be assessed.

### Remote weighing and real-time classification of phase of weight loss

A cornerstone of the ADAPT study design is the use of daily weighing to define the weight-loss phases in real time and schedule study assessments that align with participants’ individual periods of active weight loss and/or a weight loss plateau. Throughout the enrollment period, all participants are asked to weigh themselves daily on a study-provided electronic scale (BodyTrace™). Daily weights are remotely transmitted and monitored by the study. Participants are instructed to weigh themselves daily upon waking (fasted) and after voiding. Baseline weight is calculated as the average daily weight over the ~ 7-day period after the baseline visit, but before the start of the behavioral weight loss program. The baseline weight is used to calculate the daily percentage body weight change from baseline in real time.

Our pre-defined study criterion for active weight loss is based on the typically recommended pace of weight loss in a behavioral weight loss program and is defined as a rate of ≥0.5 lb/week. A weight loss plateau is defined as a rate within ±0.25 lbs/week. For each participant, daily percent weight change relative to baseline weight is calculated, and participant-specific slopes are derived that convert these percent changes into pound-per-week-equivalent rates aligned with the pre-defined study criteria for active weight loss and weight loss plateau.

The real-time slope of daily percentage of weight change over the preceding 21-day period is monitored on a rolling basis. Participants who meet or exceed their personalized calculated active weight loss slope (equivalent to ≥0.5 lb/week) for the proceeding 21-day period are eligible to be invited for an active weight loss visit once they pass a minimum time threshold of 4 weeks of participation in the behavioral weight loss program. The 4-week minimum criterion is meant to avert acquiring study outcome measures during the early weight loss phase [19]. Participants are determined to be in an involuntary weight loss plateau when their real-time slope over the preceding 21-day period meets their personalized calculated plateau slope (equivalent to within ±0.25 lbs/week; See Fig 4 A and B for representative examples). Participants are only eligible to meet plateau criteria if they previously met active weight loss criteria. When participants meet either criterion, an in-person study visit for the appropriate visit type is scheduled within two weeks.

